**8.6.1 Mandatory Samples**

The samples detailed below for PD and biomarker research are required and will be collected from all participants.

**8.6.1.1 Blood Sampling**

Blood samples will be collected for determining inhibition of IL-1β cytokine release following ex vivo LPS stimulation, cytokines levels (such as but not limited to IL-1β), and CRP level.

A mandatory whole blood sample will be taken for DNA extraction and clinical genotyping from every participant. If the sample is missed on Day 1, it can be collected at any other scheduled visit*.*

Finally, blood samples will be collected for safety exploratory biomarker assessment at baseline and In case of liver function test abnormalities (see Section 8.2.8).

**8.6.1.2 Stool Sampling**

Stool samples will be collected for determining the levels of calprotectin and may be used to assess microbiome composition and levels of cytokines or PD biomarkers (such as but not limited to IL-1β).

Volatile biomarkers may be assessed from the stool samples as well.

**8.6.1.3 Tissue Sampling**

**Rectal Biopsies**

In addition to the biopsy mentioned in Section 8.4.1 for PK assessment in tissue, additional biopsies will be collected for PD assessments as indicated in the SoAs (see Table 1).

In order to have the highest number of samples available for the most important analyses, the sequence of analysis will correspond to:

1. PD biomarker (e.g., mature IL-1β, cleaved caspase-1, etc.),

2. Hematoxylin and eosin, and immunohistochemistry,

3. Tissue PK,

4. PD biomarker (e.g., cleaved IL-18 and cleaved gasdermin D),

5. Assessment of cellular differences and function of individual cells,

6. Exploratory and/or disease biomarkers.

Biopsies should be taken from the rectal mucosa up to 15 cm from the anal verge. Rectal biopsies will be collected for the following assessments:

• PD biomarkers such as cleaved caspase-1 and mature IL-1β. Additional PD

biomarkers (such as, but not limited to, cleaved IL-18 and cleaved gasdermin D)

may be assessed.

• To characterize cell types such as but not limited to neutrophils and inflammatory monocytes. Cell types of interest may be identified through various methods such as but not limited to histology (hematoxylin and eosin staining), immunohistochemistry (specific protein staining) and fluorescence in situ hybridization (detection of gene transcripts expression).

• RNA extraction on tissue colon biopsy samples may be performed in order to undertake whole or targeted transcriptome gene expression analysis. Analysis may be performed at the single cell level.

• Bacterial DNA or RNA may be extracted for subsequent mucosa-associated metagenomic analysis*.*

**8.7 SAMPLES FOR RESEARCH BIOSAMPLE REPOSITORY**

**8.7.1 Overview of the Research Biosample Repository**

The Roche RBR is a centrally administered group of facilities for the long-term storage of human biologic samples, including body fluids, solid tissues, and derivatives thereof

(e.g., DNA, RNA, proteins, peptides). The collection, storage, and analysis of the RBR

samples will facilitate the rational design of new pharmaceutical agents and the development of diagnostic tests, which may allow for individualized drug therapy for patients in the future.

Samples for the RBR will be collected from participants who give specific consent to participate in this optional RBR. Collected RBR samples will be used to achieve the following objectives:

• To study the association of biomarkers with efficacy or progressive disease.

• To identify safety biomarkers that are associated with susceptibility to developing

AEs or can lead to improved AE monitoring or investigation.

• To increase knowledge and understanding of disease biology and drug safety.

• To study treatment response, including drug effects and the processes of drug absorption and disposition.

• To develop biomarker or diagnostic assays and establish the performance characteristics of these assays.

**8.7.2 Sample Collection**

The following samples will be stored in the RBR and used for research purposes, including, but not limited to, research on biomarkers related to RO7486967, diseases, or drug safety:

• Leftover plasma samples

• Leftover serum samples

• Leftover tissue samples and the isolated derivatives (e.g., DNA)

• Leftover blood samples and the isolated derivatives (e.g., DNA)

• Left over stool samples and isolated derivatives (e.g., DNA)

Samples may be sent to one or more laboratories for analysis of germline or somatic mutations via whole genome sequencing (WGS)/whole exome sequencing (WES), or other genomic analysis methods. Genomics is increasingly informing researchers’ understanding of disease pathobiology. WGS and WES provide a comprehensive characterization of the genome and exome, respectively, and, along with clinical data collected in this study, may increase the opportunity for developing new therapeutic approaches or new methods for monitoring efficacy and safety or predicting which patients are more likely to respond to a drug or develop AEs.

Participants will not be identified by name or any other personally identifying information. Data generated from RBR samples will be analyzed in the context of this study but may also be explored in aggregate with data from other studies. The availability of a larger dataset will assist in identification and characterization of important biomarkers and pathways to support future drug development.

If allowed by local laws, the participant may request access to the non-interpreted genomics data (from blood samples). Such a request must be conveyed to the Sponsor by the Investigator, using the email address: [[name]](mailto:[contact])[[contact].](mailto:[contact]) The information, if available at the time of the request, would be shared with the Investigator in the form of a data file of raw genomic sequencing data. The Sponsor will not provide any interpretation of this raw genomic sequencing data. The interpretation of these data will require expertise in genomic and genetic analysis and an understanding

of the variability of the technology used for data generation.

For all samples, dates of consent should be recorded on the associated RBR page of the eCRF. Details on processes for collection and shipment of these samples can be found in separate sample documentation.

RBR samples will be stored and used until no longer needed or until they are depleted. The RBR storage period will be in accordance with the IRB/EC‑approved Informed

Consent Form and applicable laws (e.g., Health Authority requirements).

The repository samples will be subject to the confidentiality standards (as described under Confidentiality and in Appendix 1).

**8.8 TIMING OF STUDY ASSESSMENTS**

**8.8.1 Screening and Pre-treatment Assessments**

Written informed consent for participation in the study must be obtained before performing any study-specific screening tests or evaluations. ICFs for enrolled participant and for participants who are not subsequently enrolled will be maintained at the study site.

All screening, and all pre-treatment assessments (related to entry criteria), must be completed and reviewed by the Investigator to confirm that participants meet all eligibility criteria. The Investigator will maintain a screening log to record details of all participants screened and to confirm eligibility or record reasons for screening failure.

An Eligibility Screening Form documenting the Investigator’s assessment of each screened participant with regard to the protocol’s inclusion and exclusion criteria is to be completed by the Investigator and kept at the investigational site.

Screening and pre-treatment assessments will be performed within 28 days prior to

Day 1, unless otherwise specified. Results of SOC tests or examinations performed prior to obtaining informed consent and within 28 days prior to Day 1 may be used and do not need to be repeated for screening.

In order to assess MCS patients will be asked to keep a diary for three consecutive days to record stool frequency and rectal bleeding.

**8.8.2 Assessments during Treatment**

Under no circumstances will participants who enroll in this study and have completed treatment as specified be permitted to be allocated a new randomization number and re-enroll in the study.

All assessments must be performed as per the SoAs (Section 1.3). Assessments scheduled on the day of study treatment administration should be performed prior to administration of study treatment, unless otherwise noted in the SoAs.

**8.8.3 Assessments at Study Completion/Early Withdrawal Visit**

Participants who complete the study (defined as completing the Day 7 visit) will be asked to return to the clinic for a follow-up visit at Day 14 (± 3 days). Participants who discontinue early will have an early withdrawal visit at the time of the withdrawal, and the follow-up visit 7 days (± 3 days) later.

**8.8.4 Follow-Up Assessments**

After the study completion/early withdrawal visit, AEs should be followed as outlined in

Sections 8.2.1 and 8.2.3.

**8.8.5 Assessments at Unscheduled Visits**

For activities that are required to be performed in case of an unscheduled visit, refer to the SoAs (Section 1.3).

**9. STATISTICAL CONSIDERATIONS**

**9.1 STATISTICAL HYPOTHESES**

No statistical hypotheses are to be tested in this study.

**9.2 SAMPLE SIZE DETERMINATION**

The study is expected to enroll approximately 18 patients in total, with 6 in the placebo arm and 12 in the treatment arm.

No formal statistical sample size calculations were performed; sample size is based on feasibility. No formal statistical analyses will be undertaken. Data will be summarized and listed as appropriate.

**9.3 POPULATIONS FOR ANALYSES**

For purposes of analysis, the following populations are defined in Table 7.

**Table 7 Analysis Populations**

**Population Description**

Intent-to-treat All randomized participants will be included in the intent-to-treat population.

Safety All participants randomized to study treatment and who received at least one dose of the study treatment, whether prematurely withdrawn from the study or not, will be included in the safety analysis.

Pharmacokinetic All participants who have received at least one dose of study treatment and who have data from at least one postdose sample will be included in the PK analysis population. Participants will be excluded from the PK analysis population if they significantly violate the inclusion or exclusion criteria, deviate significantly from the protocol, or if data are

unavailable or incomplete which may influence the PK

analysis. Excluded cases will be documented together with the reason for exclusion. All decisions on exclusions from the analysis will be made prior to database closure.

**9.4 STATISTICAL ANALYSES**

**9.4.1 Demographics and Baseline Characteristics**

Summaries for categorical baseline variables will include counts and frequencies. Summaries for continuous baseline variables will include counts, means, and standard deviations. Participants in the intent-to-treat analysis set will contribute to baseline summaries.

For each variable, the “baseline value” will be the last non-missing value obtained prior to the first administration of study treatment.

**9.4.2 Efficacy Analyses**

No efficacy analyses are planned.

**9.4.3 Safety Analyses**

All safety analyses (see Table 8) will be based on the safety analysis population grouped according to the treatment assigned at randomization.

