**Table 3 Objectives and Endpoints**

|  | **Objectives** | **Endpoints** |
| --- | --- | --- |
| **Primary** | • To assess the safety and tolerability of orally administered RO7486967 in participants with active UC.  • To investigate the PK of orally administered RO7486967 in blood of participants with active UC. | • Incidence and severity of adverse events.  • Changes in vital signs, ECG parameters, and clinical laboratory safety parameters.  • Pharmacokinetic parameters of RO7486967 (and its metabolites, as applicable) in  blood by NCA and/or population  PK analysis. |
| **Secondary** | • To evaluate the effects on inflammation markers. | • Changes in CRP in blood and calprotectin in stool. |
| **Exploratory** | • To assess changes in PD markers in tissue and in stool in response to RO7486967.  • To assess changes in cellular compositions and gene expression in rectal tissue.  • To assess the inhibition of cytokine release after lipopolysaccharide (LPS) stimulation ex vivo in blood of patients treated with RO7486967.  • To explore the association of the microbiome composition with PD and safety of RO7486967.  • To assess the concentration of RO7486967 and its metabolites, as applicable, administered orally in rectal tissue of participants with active UC. | • **Rectal Tissue**: PK and PD biomarker such as mature IL-1β, cleaved caspase-1, cleaved gasdermin D, and cellular differences and function of individual cells.  • **Stool**: PD biomarkers such as mature IL-1β, microbiome composition.  • **Blood**: Cytokines (e.g., IL-1β and IL-18), ex vivo cytokine release (e.g., IL-1β). |

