**4. STUDY DESIGN**

**4.1 OVERALL DESIGN**

Study BP43099 is a randomized, placebo-controlled, Investigator- and patient-blind, Sponsor-open study to assess safety, tolerability, and PK of RO7486967 in patients with active, moderate to severe UC. The study will utilize two treatment arms: placebo versus

450 mg RO7486967 administered orally QD.

A total of 18 participants are expected to be recruited, with approximately 12 receiving

450 mg RO7486967 and approximately 6 receiving placebo.

All participants in the study will have been diagnosed with UC previously and be in an active stage of their disease.

After the screening period, participants will be randomized to receive either placebo or RO7486967 orally (3 capsules of 150 mg). Randomization will be 2:1 (RO7486967 to placebo) and occur on Day −1. Treatment duration will be 7 days. Participants will have biopsies taken from the rectum (rectoscopy) between Day −3 and Day −1 and on Day 7 pre-dose (see Figure 1).

Participants will be hospitalized from Day −1 to Day 7. They will return to the clinic for the follow-up visit on Day 14 ± 3 days.

Dose adjustments are not foreseen during the study.

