**4.2.3 Rationale for Control Group**

RO7486967 will be compared against a placebo-concurrent control, with participants randomized in a 2:1 ratio to QD, oral administrations of RO7486967 or placebo, respectively. A placebo arm will be employed in order to derive a preliminary

assessment of the safety risk of RO7486967 in participants with UC and for equipoise in discriminating drug-relatedness of AEs. A placebo group will similarly inform the analysis of key biomarkers, including histopathologic changes in colonic biopsy samples and biomarkers used to establish PD effect.

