**6.4 TREATMENT COMPLIANCE**

The qualified individual responsible for dispensing the study treatment will prepare the correct dose according to the randomization schedule. This individual will write the date dispensed and participant number on the study treatment container label and on the Drug Accountability Record. This individual will also record the study treatment number received by each participant during the study and record the returned number of capsules on the Drug Accountability Record.

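### Safety tables are grouped by assigned arm, so a known wrong-treatment error would leave that participant's primary safety data in the wrong group; a minor, near-free correction

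*Combined protocol and SAP*

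**What the plan says.** Section 9.4.3 sets the rule for every safety output: "All safety analyses (see Table 8) will be based on the safety analysis population grouped according to the treatment assigned at randomization". Table 7 (Section 9.3) defines that population as "All participants randomized to study treatment and who received at least one dose of the study treatment", whether or not they later withdrew. It does not say where to place a participant whose received treatment differs from the assigned one, and no other section supplies an as-received safety analysis.

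The first primary endpoint in Table 3 is "Incidence and severity of adverse events". Section 4.2.3 explains the placebo arm as giving a preliminary "assessment of the safety risk of RO7486967 in participants with UC and for equipoise in discriminating drug-relatedness of AEs". Section 9.1 adds "No statistical hypotheses are to be tested in this study", and Section 9.4.2 plans no efficacy analysis.

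On dosing, Section 6.4 says that the person dispensing "will prepare the correct dose according to the randomization schedule". Appendix 2, Section 5.2 gives recording rules for medication errors and includes administration of the wrong drug among its examples. Section 9.5 lists all protocol deviations and all treatment administration.

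**The concern.** Membership of the safety population depends on exposure, but the grouping within it depends on assignment. These agree unless someone is given the other arm's treatment. When they disagree, the safety question follows exposure: the placebo group is there to show what happens without the drug.

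Grouping by assignment is usually defended because it protects a randomized efficacy comparison. That defence has little force here, since no efficacy analysis and no test are planned. If the drug raises an event rate, misclassification in either direction pulls the two arms together in expectation, which for safety is the unhelpful direction. With six placebo participants, one misplaced person is a visible share of the reference group.

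There is also a case for settling this in advance. The study is Sponsor-open, and Section 6.3.1 makes the randomization list available to the sponsor's statisticians or programmers. Regrouping safety data after an error came to light would be a post hoc departure by people who may hold the codes.

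**Working it through.** **Inputs.** Section 9.2: "The study is expected to enroll approximately 18 patients in total, with 6 in the placebo arm and 12 in the treatment arm". Section 4.1: 2:1 allocation. Section 2.3: 4 of 18 healthy volunteers given RO7486967 in the multiple-dose part of the earlier study had a mild transaminase increase. This is used only as an illustrative rate on drug. The documents give no wrong-treatment rate and no placebo event rate, so any values used for these are assumptions.

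**Plan's own figure.** 18 × 2/3 = 12 and 18 × 1/3 = 6. The stated split reproduces.

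**Expected difference under assigned-arm grouping.** Let pD and pP be the event rates on drug and placebo. Assume the mis-dosed participant takes the other treatment throughout; fewer wrong doses would presumably mean less distortion.

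- Placebo-assigned takes drug: pD − (5pP + pD)/6 = (5/6)(pD − pP).
- Drug-assigned takes placebo: (11pD + pP)/12 − pP = (11/12)(pD − pP).
- Swap: (11pD + pP)/12 − (5pP + pD)/6 = (9/12)(pD − pP).

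| Error | Loss of true difference | Shown if pD = 4/18 = 22.2%, pP = 0% (assumed) | Active/placebo denominators as received |
|---|---|---|---|
| Placebo-assigned takes drug | 1/6 = 16.7% | 18.5 points | 13/5 |
| Drug-assigned takes placebo | 1/12 = 8.3% | 20.4 points | 11/7 |
| Swap | 1/4 = 25.0% | 16.7 points | 12/6 |

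The proportional losses do not depend on pD or pP. Grouping by treatment received restores the expected difference to pD − pP, here 22.2 points.

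**When the direction reverses.** Suppose the mis-dosed placebo-assigned participant has an event and none of the other five placebo participants does.

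| Events among 12 active | As assigned: placebo v active | As received: placebo v active | Result |
|---|---|---|---|
| 0 | 1/6 (16.7%) v 0/12 (0%) | 0/5 v 1/13 (7.7%) | Reversed |
| 1 | 1/6 (16.7%) v 1/12 (8.3%) | 0/5 v 2/13 (15.4%) | Reversed |
| 2 | 1/6 (16.7%) v 2/12 (16.7%) | 0/5 v 3/13 (23.1%) | Tie as assigned |
| 3 | 1/6 (16.7%) v 3/12 (25.0%) | 0/5 v 4/13 (30.8%) | Same direction |

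The limit of 0 or 1 belongs to this case. If one of the other five placebo participants also has the event, the reversing counts move to 2 and 3; for example, 2/6 (33.3%) v 3/12 (25.0%) as assigned becomes 1/5 (20.0%) v 4/13 (30.8%) as received.

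**Chance of an error.** With an assumed per-participant rate e, P(at least one among n) = 1 − (1 − e)^n. For e from 0.5% to 5% this is 8.6% to 60.3% among 18 participants and 3.0% to 26.5% among the 6 on placebo. The width of the range shows only that the documents do not settle the matter.

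**The case against.** The strongest reply is that little would follow in practice. Assignment is central by IxRS (Section 6.3.1), capsules arrive from the sponsor in labelled containers (Table 4), dosing is supervised at the study center (Section 6), and the treatment number each participant receives is recorded (Section 6.4). Deviations and treatment administration are listed (Section 9.5), laboratory results are shown individually (Table 8), and wrong-drug events go on the adverse event form (Appendix 2, Section 5.2). With 18 participants, a reader would see a known error. The study-level and individual stopping criteria (Sections 4.1.2 and 4.1.3) work from events judged related, abnormal results and clinical judgement; none uses the arm-level table. All of this stands, and it limits the severity. None of it regroups the adverse event, laboratory, vital-sign or ECG summaries.

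A simple rule that any dose of RO7486967 moves a participant wholly to the drug group has its own fault: it would carry over events that began before the erroneous dose. That objection also stands, and the fix below allows for it.

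A reader might infer that routine PK results would expose a placebo participant who had taken drug and so contradict the safety tables. Section 8.4 does not support this, because samples from placebo-treated participants are not assayed in the first instance. For the same reason, grouping by treatment received corrects only errors that are detected.

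**Conclusion.** The point holds as a minor correction. Section 9.4.3 applies assigned-arm grouping to a primary safety question about exposure, and nothing elsewhere in the protocol overrides it. Given one full-course wrong-treatment error, the expected drug-minus-placebo difference shrinks by 8.3% to 16.7%, or by 25.0% for a swap. The choice of grouping has no effect without a detected mix-up. The analysis is descriptive, so no type I error or power is involved.

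Three stronger readings are tempting and not supported:

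- That every dosing mix-up credits drug effects to placebo. Only a placebo-assigned participant given RO7486967, alone or in a swap, does that. The opposite error dilutes the active arm, and timing errors or overdoses do not change the group.
- That the comparison would generally reverse. In the case tabulated, it needs 0 or 1 events among the 12 active participants.
- That errors are likely because the site prepares doses. Section 6.4 says only that doses are prepared to the schedule, and recording rules for errors do not show that errors are expected.

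**What to change.** In Section 9.4.3, replace grouping by assigned arm with grouping by *treatment actually received*. Add a rule for a participant who receives both treatments: events with onset at or after the first RO7486967 dose count under RO7486967, earlier events do not, and the participant is flagged in the tables with a footnote saying how they enter the denominators. Keep assigned-arm grouping for the intent-to-treat baseline summaries in Section 9.4.1.

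The cost is two or three sentences. No data collection changes, and if no wrong-treatment error is found the outputs are identical. The Section 9.5 listings already cover deviations and administration, so no separate listing is needed.
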